## Abstract

**Background:**

Rural communities experience unique barriers to food access when compared to urban areas and food security is a public health issue in rural, high poverty communities. A multi-leveled socio-ecological intervention to develop food policy councils (FPCs), and improve food security in rural communities was created. Methods to carry out such an intervention were developed and are described.

**Methods:**

A longitudinal, matched treatment and comparison study was conducted in 24 rural, high poverty counties in South Dakota, Indiana, Missouri, Michigan, Nebraska and Ohio. Counties were assigned to a treatment (*n* = 12) or comparison (n = 12) group. Intervention activities focus on three key components that impact food security: 1) community coaching by Extension Educators/field staff, 2) FPC development, and 3) development of a *MyChoice* food pantry. Community coaching was only provided to intervention counties. Evaluation components focus on three levels of the intervention: 1) Community (FPCs), 2) Food Pantry Organization, and 3) Pantry Client & Families. Participants in this study were community stakeholders, food pantry directors, staff/volunteers and food pantry clients. Pantry food access/availability including pantry food quality and quantity, household food security and pantry client dietary intake are dependent variables.

**Discussion:**

The results of this study will provide a framework for utilizing a multi-leveled socio-ecological intervention with the purpose of improving food security in rural, high poverty communities. Additionally, the results of this study will yield evidence-based best practices and tools for both FPC development and the transition to a guided-client choice model of distribution in food pantries.

**Trial registration:**

ClinicalTrials.gov; NCT03566095. Retrospectively registered on June, 21, 2018.

## Background

Food security has been defined as “access by all people at all times to enough food for an active, healthy life” [1] and “includes the ready availability of nutritionally adequate, safe foods, and the assured ability to acquire them in socially acceptable ways.” [2] Rural communities (often characterized by a population of 2500 persons or less) [3] experience unique barriers to food access when compared to urban areas, including, but not limited to, access and affordability of fruits and vegetables, [4] lack of transportation, [5] and chronic disease [6]. Communities with increased food insecurity prevalence when compared with the national average, may have a higher need for nutrition assistance, specifically food pantry services [7]. Integration of guided client-choice within pantries, development of food policy councils (FPCs) in communities, and support from community coaches may be a way to address food insecurity in rural, Midwestern areas.

Most food pantry users are food insecure, which is linked with being overweight and is often associated with diet-related co-morbidities [8]. Food insecure individuals may avoid hunger by consuming low-cost and shelf-stable foods, eating a small variety of foods, and/or binging when food is abundant [9]. Because certain characteristics and food insecurity predispose individuals to diet-related co-morbidities, ensuring that food pantries are able to provide nutrient-rich foods to the food insecure population in rural communities is crucial. Guided client-choice is a model of distribution in which pantry clients choose the foods they would like from the pantry based upon family size and is formatted based upon USDA MyPlate [10]. The guided client-choice style of food distribution in food pantries has been shown to serve the needs of the food pantry clients better when compared to the traditional model of distribution (pre-selected box or bag) [11]. This model reduces the amount of waste spurred by unwanted food items not being used and offers a more dignified experience by allowing pantry clients to choose foods that will supplement their diets [11]. Thus, when using a guided client choice model of distribution, food pantries have the potential to address the nutritional needs of the food insecure population.

FPCs have the potential to improve the nutritional quality of available food, affect federal-, state-, and local-level policy, systems and environmental efforts, and connect a diverse network of ‘food’ stakeholders from the public, private and nonprofit sectors, which includes local food pantries [12, 13]. While FPCs have been shown anecdotally to be effective in addressing food system and food security issues in urban areas [12], effectiveness has not been scientifically quantified. Furthermore, the use of FPCs as an intervention to improve food security in rural communities has not been evaluated. Since FPCs are comprised of food systems stakeholders including food pantries, it is plausible that FPCs could support emergency food operations in rural communities, and positively impact food pantry client household food security.

Community coaching is a strategy that helps community leaders plan for and overcome challenges to community development [14]. Community development work is most effective when interventions are locally conceived, locally led, and consistent with the cultural identity of the community [15]. Community coaches can effectively support community development through capacity building, fostering a collaborative environment, problem solving, reframing operating systems, transitioning to new leadership, and negotiating partnerships. Previous coaching success in sustaining community change has led some Cooperative Extension systems to recognize community coaching as a viable approach to driving sustainable community work and to institutionalize coaching as a value-added component of their work. Thus, utilizing Extension Specialists/field staff as community coaches may be an effective way to aid in the development and formation of FPCs in rural communities as they seek to develop long-term visions and goals to improve food security.

Six states (Indiana, Michigan, Missouri, Nebraska, Ohio, and South Dakota) have combined efforts to implement an integrated, community-led intervention in diverse, rural, high poverty Midwestern counties to enhance food security, called *Voices for Food*. A trans-disciplinary team of specialists in nutrition, agriculture, youth, community development, evaluation, and researchers from the Cooperative Extension North Central Region, developed *Voices for Food*. *Voices for Food* is a five-year integrated Extension and research project guided by the Social-Ecological Model of Behavior Change^12^ that addresses the United States Department of Agriculture (USDA), Agriculture and Food Research Initiative (AFRI) Food Security Challenge Area. The project team uses a multifaceted approach to promote socio-ecological changes in rural communities to increase access to, availability of, and consumption of nutritious foods. The project team selected rural communities with high poverty rates to engage with community coaches in order to: 1) develop new or provide support to existing FPCs and 2) encourage FPCs to make socio-ecological changes in their communities to increase the availability of, and access to, healthy food, which includes transitioning food pantries toward guided client choice systems. The specific project hypotheses are that: 1) having Extension Educators/field staff engaged with communities as community coaches will lead to the establishment or strengthening of multi-stakeholder FPCs working on goals to improve healthy food access within the community, and 2) in those communities that have stronger FPCs that support food pantries in transitioning to a guided client choice model called *MyChoice*, there will be greater improvement in availability of healthy foods for pantry users leading to improvement in their food security and intake of healthy foods. The purpose of this manuscript is to describe the methodology used to achieve these goals and assess the identified hypotheses.

## Methods/design

### Study design

*Voices for Food* used a longitudinal matched intervention and comparison design. Two matched treatment and comparison communities per state (*n* = 24) were selected to participate in the study based upon community and food pantry attributes. Institutional Review Board approval was obtained for this study prior to all intervention activities.

*Voices for Food* utilized the *Voices for Food Model of Behavior Change* (Fig. 1) to guide implementation activities. To address the hypotheses, *Voices for Food* focused on two key components that work together to impact food security in selected treatment communities: 1) Community coaching by Extension Educators/field staff, 2) provision of *Voices for Food* materials that describe, a) FPC development and/or support, and b) the transition to a *MyChoice* food pantry. In comparison communities, *Voices for Food* activities focused on one component: the provision of a *Voices for Food* materials that describes, a) FPC development and/or support, and b) development of a *MyChoice* food pantry*.* The notable difference between the treatment and comparison communities is that comparison communities did not receive coaching from a community coach throughout the implementation of Voices for Food. All participants in both treatment and comparison groups were blinded to the intervention. There were no circumstances in which unblinding was permissible.

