## Community & pantry recruitment

### Food pantry

Pantry directors were invited to participate through an invitational letter. Upon confirmation, the coach scheduled an in-person meeting with the pantry director to discuss project details and explain the Memorandum of Understanding (MOU), which was signed upon agreement to participate. Once the treatment food pantries were recruited, project staff followed the same protocol in matched comparison communities.

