### Community-level assessment tools

#### Community stakeholders survey

A 23-question *Community Stakeholders Survey* assessed community stakeholder perceptions in participating communities. This survey collected demographic information, perceptions of food security in the community, past experience with FPCs or similar organizations and feedback on the *Voices for Food: Food Council Guide*, and experience with the community coach.

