#### Food pantry MyChoice observation tool

A 15-question *Food Pantry MyChoice Observation Tool*, was completed by project staff, documented the extent to which key components of the *MyChoice* food pantry model were physically in place at the pantry and part of the food, food display, and distribution process.

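### The article says every participant was blinded, which cannot be true of the coached directors, champions and council stakeholders

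*Protocol article*

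**What the plan says.** Under Study design the protocol article states that "All participants in both treatment and comparison groups were blinded to the intervention". It adds: "There were no circumstances in which unblinding was permissible". Neither sentence is limited to a class of participant, and neither says what was concealed or how.

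The Methods part of the abstract defines the people concerned: "Participants in this study were community stakeholders, food pantry directors, staff/volunteers and food pantry clients". It also says: "Community coaching was only provided to intervention counties". Study design names the same contrast as the notable difference between arms: "comparison communities did not receive coaching from a community coach throughout the implementation of Voices for Food". Under Materials, both arms receive the council guide, the pantry toolkit and access to mini-grants.

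The Community Stakeholders Survey is described as collecting, among other things, "experience with the community coach". The MyChoice Observation Tool "was completed by project staff, documented the extent to which key components" of the model were in place. No masking of the people who collect data is claimed or described.

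**The concern.** A statement that all participants were blinded tells a reader that knowledge of the arm cannot have shaped what participants reported. If some knew they were being coached, that protection is absent for their answers. Perceptions of community food security, feedback on the materials and accounts of council progress are the kinds of report that expectation can move.

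The article describes matching of communities and mentions no random assignment, so the comparison already depends on how well the matching worked. A blinding claim is one of the few further safeguards that a reader or systematic reviewer could credit to the study. If the claim is wrong, the risk of bias in participant-reported outcomes will be rated too low.

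**Working it through.** The point rests on no figure, so there is nothing to recompute. The check compares the blinding statement with what the article says about each class of participant.

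1. **What would have to be concealed.** Both arms get the same written materials and mini-grant access. The only difference named is coaching, so being blinded to the intervention has to mean being unaware of coaching. No sham coach and no concealment procedure are described.

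2. **Community champions.** The Community champion section says they are recruited in order to receive coaching for council development. A champion in a treatment community cannot be unaware of it.

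3. **Pantry directors.** The Training tracking form section refers to Extension coaching assistance given to the intervention pantries. The director runs the pantry that receives it and cannot be unaware of it.

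4. **Council stakeholders.** Under the first hypothesis, coaches engaged with the community establish or strengthen the council. Members of a coached council work with the coach, and their survey asks about that experience. Nobody can report on a coach while unaware of the coaching. Where no council had formed, stakeholders were drawn from the wider community, and the argument is weaker for them.

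5. **Pantry staff and volunteers.** They work in the coached pantry and take part in its change of distribution model. Unawareness is unlikely, although the article does not describe their individual contact with the coach.

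6. **Clients.** No section describes contact between clients and the coach. They could have been unaware of coaching or of a comparison arm. The article neither shows this nor rules it out.

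7. **Where it bears on the analysis.** Table 1 lists ten tools. Three are surveys answered by stakeholders, directors and staff or volunteers. For two more, the council tracking form and the training tracking form, Table 1 gives the champion or director as the subject. That makes 3 + 2 = 5 of 10. The count is approximate, because the same column gives project staff as the subject of surveys that participants answer. Three of these five (the stakeholder survey and the two tracking forms) are among the tools named in Statistical analysis for the first hypothesis. The tools named for the second are the inventory log, the food box log, the dietary recall and the MyChoice observation.

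The word *all* therefore fails for directors, champions and council stakeholders in the treatment arm, is doubtful for pantry staff and volunteers, and is undetermined for clients.

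**The case against.** The best defence is that the authors meant something narrower: participants were not told that another arm existed, or what the hypotheses were. That is possible, and for clients it may be true. It matters, because the client food security score drives the sample size, and food security and diet are among the listed dependent variables. But the text says blinded to the intervention and applies this to everyone, so the defence limits the error without removing it.

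The recruitment meetings are not evidence against blinding. The coach meets the director to go through the project and a memorandum of understanding, but the article says the same procedure was followed in comparison communities, and champions in both arms had such a meeting. Signing the memorandum reveals nothing about the arm. Only the coaching and the survey item carry the point.

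A reader might also infer that the article falsely claims blinded assessors, or that the staff who rated the MyChoice tool knew the arm. The documents support neither. The blinding sentence speaks of participants only. Project staff recorded the coaching and project staff completed the tool, but nothing says they were the same people, and the Discussion describes many personnel in six states. Knowledge of the arm is plausible but not documented.

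Finally, the Community champion section can be read as offering coaching to champions in both arms. That conflicts with the abstract and with Study design and needs its own reconciliation. It does not rescue the blinding claim, since a champion who is coached is aware of it in either arm.

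**Conclusion.** The concern holds in a limited form. The unqualified statement cannot be true of directors, champions and council stakeholders in treatment communities, and is unlikely for pantry staff and volunteers. For clients, unawareness is possible but unsupported. It would go too far to say that nobody was blinded, or that client-reported food security and diet are shown to be affected.

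The size of any bias cannot be derived from the article. The exposure is clearest in the participant-reported tools behind the first hypothesis. No sample size, power figure or analysis model changes. The conclusion assumes that coaching was delivered as the abstract and Study design describe, in treatment communities only and without concealment. This should be corrected, because it changes how far some outcomes can be trusted and costs very little to put right.

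**What to change.** Replace the two sentences under Study design with a statement that:

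- pantry directors, staff and volunteers, community champions and council stakeholders were not blinded to coaching;
- sets out what, if anything, was withheld from clients (for example the existence of the other arm) and how;
- says whether the people who collected data knew the arm, as a matter of fact either way.

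In the conclusions, treat outcomes reported by stakeholders, directors and staff as open-label and list this as a limitation. Do not credit the MyChoice observation with masking unless it was actually masked. Reconcile the Community champion section with the statements that coaching went to one arm only.

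One optional safeguard is available. The inventory log and food box log sections speak of food codes that will be assigned. Where that coding is still to be done, arm and pantry identity can be removed from the coders' files. The article shows no bias in the coding, so this is a precaution.

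The text changes cost a few lines. The optional step costs the preparation of de-identified files.

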**Fig. 1 Fig1:**
[figure not shown]
Voices for Food Model of Behavior Change

### Materials

To guide the development or strengthening of FPCs in both intervention and comparison communities, the project team developed a the *Voices for Food: Food Council Creation Guide*, which includes information on the following topics: importance of engaging FPCs in food systems work; how to develop/sustain a FPC; networking and communicating with stakeholders; developing a FPC structure; partnering with food banks and pantries; working with the agricultural community; finances; and community food assessments. The guide also provides information regarding the opportunity to apply for mini-grant funds provided by *Voices for Food*. Mini-grant funds were available to all intervention and comparison communities, which required collaboration between the FPC and pantry and consistency with *Voices for Food* goals. All communities had the opportunity to submit a budget plan and justification, which was vetted and approved by the *Voices for Food* PD leadership team.

To guide the transition to *MyChoice* in the food pantry in both intervention and comparison communities, the project team developed a *Voices for Food: Food Pantry Toolkit* which includes information on the following topics: implementing the *MyChoice* guided client-choice model of distribution, a *Voices for Food* Ambassador’s Training (includes Nutrition Education [16], Food Safety Training [17], and Cultural Competency Training [18]), shelf talkers (labels), and USDA MyPlate materials. Nutrition education [16] were delivered in partnership with SNAP-Ed as an approved, evidence based curriculum was used for this portion [19, 20]. Both Food Safety [17] and Cultural Competency Training [18] were delivered and completed by pantry staff using the resources included in the toolkit.

### Identifying communities

Criteria were developed to identify eligible communities for the study. Eligible communities were those located in counties defined as non-metro with poverty rates > 16% [21], those that have a Cooperative Extension presence, do not have a well established FPC or similar organization in place, and do not already have a full guided client-choice model in their local food pantry in place.

### Matching intervention and comparison communities

Prior to recruitment, intervention and comparison communities were matched based upon the criteria for identifying communities and the characteristics of the local food pantry in the community. Pantry characteristics that aided in matching communities were: physical location, distance to another potential pantry, administering organization, hours and days of operation, level of client-choice, interest in study participation and working with Cooperative Extension, number of households served, an estimate of long-term pantry users (greater than 2 years), pounds of food distributed per month, government commodity program assistance (e.g. The Emergency Food Assistance Program [TEFAP], Food Distribution Program on Indian Reservations [FDPIR], and Commodity Supplemental Food Program [CSFP], food bank partnership, infrastructure and capacity (storage, shelving, etc.), and predominant racial/ethnic group served at the pantry.

## Community & pantry recruitment

### Food pantry

Pantry directors were invited to participate through an invitational letter. Upon confirmation, the coach scheduled an in-person meeting with the pantry director to discuss project details and explain the Memorandum of Understanding (MOU), which was signed upon agreement to participate. Once the treatment food pantries were recruited, project staff followed the same protocol in matched comparison communities.

### Community champion

Community champions were recruited to receive coaching for FPC development in the implementation of *Voices for Food* in both treatment and comparison communities. With the assistance of the pantry directors, a list of potential local community champions and stakeholders was created. A letter was sent to the potential community champion in each community to introduce the project, identify the participating pantry, to inquire about interest in assisting with *Voices for Food* and to request confirmation of participation. Upon confirmation of participation, an in-person meeting was scheduled by the coach with the community champion to discuss project details and the MOU, which was signed upon agreement to participate.

## Measures

### Organization/scheduling data collection

Quantitative and qualitative data were collected Fall Year 02 (Y02; pre-intervention), Fall Year 04 (Y04; mid-intervention) and Fall Year 05 (Y05; post-intervention) from community stakeholders, food pantry directors, food pantry staff/volunteers, and food pantry clients. A longer timeframe between pre-intervention and mid-intervention data collection was observed to allow more time for the treatment activities to be implemented.

